### Methods for additional analyses (e.g. subgroup analyses) {27d}

A per-protocol analysis will be conducted as a secondary analysis. No formal subgroup analyses are planned. All additional analyses beyond the pre-specified hierarchical testing strategy will be considered exploratory.

### Interim analyses {28b}

No formal interim analyses or stopping guidelines are planned. The early analysis conducted at week 12 is limited to selected secondary endpoints and will not influence decisions regarding trial continuation or termination.

### Protocol and statistical analysis plan {5}

The full trial protocol, including the pre-specified statistical analysis plan, is published with this manuscript.

## Oversight and monitoring

### Composition of the coordinating centre and Trial Steering Committee {3d}

The trial is coordinated by the sponsor, Medical University of Vienna, which is responsible for overall trial management, regulatory compliance, communication with participating sites and day-to-day operational support. The coordinating team meets with co-sponsors bi-weekly to review recruitment, data quality, and operational issues.

A Trial Steering Committee (TSC) provides overall scientific oversight of the trial. The TSC is responsible for monitoring trial progress, adherence to the protocol, and safeguarding the scientific integrity of the study. The committee meets at least once monthly over the course of the trial and provides guidance to the participating centres as required. No independent endpoint adjudication committee is planned, as outcome assessment is performed by blinded joint assessors according to predefined criteria.

### Composition of the data monitoring committee, its role and reporting structure {28a}

Given the low-risk nature of the intervention, a formal independent Data and Safety Monitoring Board (DSMB) has not been established. Safety oversight is ensured by the principal investigator and study personnel, with systematic recording and assessment of adverse events, timely reporting of serious adverse events, and external oversight via local monitors, CTIS, and potential regulatory or ethics committee inspections.

### Frequency and plans for auditing trial conduct {29}

Trial conduct and data quality are monitored on a regular basis by the respective co-sponsor. Monitoring activities include review of data completeness and consistency, verification of key study variables, and assessment of protocol compliance. Audits by institutional or regulatory authorities may be conducted at any time. No additional independent auditing procedures are planned.

### Protocol amendments {31}

To address slow patient enrolment, the potential patient pool was expanded by changing the exclusion criterion number 2 from “Ongoing or previous therapy with any biological DiseaseModifying Anti-Rheumatic Drug (bDMARDs) or targeted synthetic DMARDs (tsDMARDs) or conventional synthetic DMARDs (csDMARDs) other than methotrexate and Hydroxychloroquine” to “Ongoing or previous therapy with any targeted synthetic DMARDs (tsDMARD) or biological Disease-Modifying Anti-Rheumatic Drug (bDMARD) with the exception of any TNFα inhibitor in a stable dose and interval for at least 4 months; We allow ongoing or previous therapy with a conventional synthetic DMARD (csDMARD) with a stable dose in the past 4 months”. Also, the visit week 8 was removed from the schedule to minimise the burden of frequent visits for patients. The future study timelines were adapted according to the regulatory delay and recruitment rates. Albumin was added to the chemistry parameters as a relevant factor for MTX metabolite analysis. Two new cosponsor centres were added: Milan, Italy, and Bucharest, Romania.

Any further protocol amendments will be submitted for review and approval by the relevant authorities listed above and information updated on ClinicalTrials.gov.

### Dissemination policy {8}

Trial results will be disseminated through peer-reviewed publications, scientific presentations and reporting in the trial registry, with study findings made available to participants on request.

## Discussion

Despite the fact that MTX is proven to be safe, efficient and cost-effective, it is likely that it does not achieve its full potential in clinical practice. The results of this trial will provide further insights into the clinical efficacy of the subcutaneous versus oral MTX when increased to 25 mg weekly in patients with active rheumatoid arthritis, who are naïve to b/tsDMARDs. Our aim is to generate data that support clinical decision-making in optimisation of MTX dosing and administration routes for patients not being on target, and to establish evidence on novel biomarkers and their association with efficacy, hopefully paving the way for personalised MTX treatment strategies.

The MethMax trial is an investigator-initiated trial, part of Horizon Europe and funded by the Squeeze project. The Squeeze project initiative aims to optimise the use of existing therapies for rheumatic diseases through three distinct clinical trials, including MethMax. By including seven different European countries (Austria, Sweden, Norway, Netherlands, Italy, Romania and the UK), this trial covers diverse geographical patient pools, health care settings, and socioeconomic aspects of MTX prescription.

There are multiple reasons, which might limit the efficacy of oral MTX therapy: insufficient dosing, inadequate treatment adherence and subsequent potentially premature switch to b/tsDMARDs. In MethMax, we aim to address all these issues. Factors affecting patients’ treatment adherence may include side effects, the complexity of drug regimens or inadequate communication between physician and patient regarding the disease progression and treatment plan [34]. To truly compare the therapy effects of oral and subcutaneous arm based solely on their pharmacological effects and not on differences in treatment adherence that could exist, we will monitor thoroughly, and potentially even raise treatment adherence by using patient medication diaries, adherence questionnaires, digital medication tracking as well as objective methods like biomarkers. None of the existing standard methods to measure DMARD adherence is free from limitations; therefore, a combination of these three complementary measures will increase validity and reliability. To achieve this, the BAASIS questionnaire [35], originally validated in cohorts of organ-transplanted patients and used in multiple trials assessing adherence [36], was adapted to MethMax. This trial will be the first study to investigate the BAASIS-MTX, an adapted version to specifically assess MTX adherence. Importantly, we expect that the sum of adherence measurement methods used in this trial will increase the interpretation of clinical outcomes.

MTX-PGs have been investigated as active intracellular metabolites which could be utilised as a predictor of clinical outcomes and individual treatment response characteristics. Given the low concentrations of these metabolites in red blood cells and their limited stability, test methods allowing further use paired with thorough pre-analytics and logistics are necessary in clinical trials. Ongoing research is currently investigating TDM with individual MTX dosing based on MTX-PG_3–5_ levels and factors identifying MTX exposure–response association [37]. One recent study in particular in MTX-naïve patients started on MTX showed that higher MTX-PG concentrations were an independent factor for lower disease activity in MTX monotherapy, but not after adalimumab initiation in patients with continued MTX dose [38]. Thus, more data is needed to explore the behaviour of MTX metabolites with different therapy regimens.

Overall, the strength of the MethMax trial lies in its study design and procedures, combining multiple objective and subjective measurements of disease activity, patient outcomes and treatment adherence. The efforts to maximise the therapy adherence should deliver more representative results on the true pharmacological effects of MTX in its distinct routes. The main limitations of this study could include recruitment problems due to the relatively stringent inclusion/exclusion criteria, reliance on self-reported and self-performed data, and the impact of daily variations of subjective disease activity, especially in patients with an initial low disease activity score. Furthermore, patients and physicians are unblinded to the treatment allocation, and only joint assessment is performed by blinded personnel.

The anticipated results might bring valuable knowledge about the “maximisation” of the MTX therapy potential in patients with RA, providing recommendations on the optimal dose and administration route.

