### Participant timeline {18}

The study flow chart is outlined in Fig. 1 and the study related assessments in Table 2 (SPIRIT figure). After the screening and baseline visits, patients undergo scheduled study visits at weeks 4, 12, 16 and 24 (± 7 days). At each visit, a blinded joint assessment, patient reported outcomes as well as inflammatory and safety laboratory parameters are performed. Patients are asked to complete three questionnaires: Health Assessment Questionnaire Disability Index (HAQ-DI), the 36-Item Short Form Survey (SF-36) and Functional Assessment of Chronic Illness Therapy (FACIT-Fatigue) to assess the patient-reported outcomes of disease activity and quality of life three times during the study period. At predefined timepoints, drug monitoring is conducted using measurements of MTX-metabolites and TTV in blood. The medication adherence is assessed via an electronic and paper-based adherence assessments and exploratory laboratory measurements. In total, patients undergoing all scheduled study visits remain in the trial for 24 weeks, when primary endpoint is assessed.

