**Efficacy Assessments**						
Swollen joint count [31]	**x**	**x**	**x**	**x**	**x**	**x**
Tender joint count [31]	**x**	**x**	**x**	**x**	**x**	**x**
Evaluator global assessment (EGA)	**x**	**x**	**x**	**x**	**x**	**x**
Patient global assessment (PGA)	**x**	**x**	**x**	**x**	**x**	**x**
Patient pain assessment (on NRS)	**x**	**x**	**x**	**x**	**x**	**x**
Morning Stiffness (duration and on NRS)	**x**	**x**	**x**	**x**	**x**	**x**
Fatigue (on NRS)	**x**	**x**	**x**	**x**	**x**	**x**
Efficacy assessment CDAI change*			**x**	**x**	**x**	**x**
Efficacy assessment joint count change 20%*				**x**	**x**	**x**
FACIT-Fatigue Questionnaire		**x**		**x**		**x**
Quality of Life Questionnaire SF-36.v1		**x**		**x**		**x**
Disability Scale Questionnaire HAQ-DI		**x**		**x**		**x**
Adherence questionnaire BAASIS-MTX-visit specific		**x**	**x**	**x**	**x**	**x**
RheumaBuddy App use weekly (consent needed)		**x**	**x**	**x**	**x**	**x**
Patient diary MTX and folic acid weekly		**x**	**x**	**x**	**x**	**x**
Patient diary glucocorticoids daily		**x**	**x**	**(x)**	**(x)**	**(x)**

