## Assignment of interventions: blinding

### Who will be blinded {24a}

Joint assessors performing outcome measurements are blinded to participants’ study assignments. Patients, care providers and personnel performing randomisation are not blinded.

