## Data collection and management

### Plans for assessment and collection of outcomes {25a}

The following data is collected: demography (age, sex, height, weight, body mass index, ethnic origin, and childbearing potential), medical history (RA, relevant comorbidities), medication history (MTX, folic acid, GC, NSAID and other concomitant medication), disease activity of RA (pain, stiffness, patient global assessment, evaluator global assessment, tender joints, swollen joints, CDAI) and physical examination. The quality of life and subjective disease assessments are performed using questionnaires: HAQ-DI, SF-36 and FACIT-Fatigue. The treatment adherence is assessed with the Basel Assessment of Adherence to Immunosuppressive Medication Scale (BAASIS)-MTX questionnaire, entries within the mobile application RheumaBuddy and the measurement of biomarkers. Haematologic laboratory parameters include red blood cell count (RBC), haemoglobin (Hb), haematocrit (Hct), white blood cell count (WBC), platelet count (PLT). The serum chemistry includes creatinine (Crea), blood urea nitrogen (BUN), estimated glomerular filtration rate (eGFR), creatine kinase (CK), lactate dehydrogenase (LDH), alanine aminotransferase (ALT), aspartate aminotransferase (AST), gamma-glutamyl transferase (GGT), alkaline phosphatase (AP), total bilirubin and albumin. Tests for hepatitis B and C, as well as the rheumatoid factor and anti-CCP antibodies, are performed at screening, unless there is an available result less than 6 months old. Pregnancy test is performed in women of childbearing potential at each study visit at the centre as either urinary or blood test, except for a urinary test at home at weeks 8 and 20, which is self-reported in a diary. Vital signs are assessed regularly.

Exploratory laboratory assessments include the plasma metabolites MTX and 7-hydroxymethotrexate (7-OHMTX), the intracellular MTX-PGs, TTV in plasma, as well as finger sweat.

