## Statistical methods

### Statistical methods for primary and secondary outcomes {27a}

The null hypothesis is as follows: The use of 25 mg SCMTX is not superior to 25 mg POMTX weekly in patients with active RA, previously treated with POMTX.

The primary endpoint, defined as the proportion of patients achieving CDAI remission at week 24, will be compared between treatment groups using a *χ*^2^ test. A Fisher’s exact test will be used if the endpoint occurs in fewer than five patients in any group. Superiority of the subcutaneous MTX arm will be tested at a two-sided alpha level of 0.05.

Secondary categorical outcomes will be analysed using *χ*^2^ tests (or Fisher’s exact tests where appropriate), and non-normally distributed continuous outcomes will be analysed using the Mann–Whitney *U* test. For categorical variables, absolute frequencies and percentages will be reported. Time to CDAI remission will be analysed using Kaplan–Meier curves, reporting medians and interquartile ranges, and compared between treatment groups using a log-rank test.

Secondary endpoints will be tested in a pre-specified stepwise hierarchical order until the first non-significant result is reached. All outcomes tested thereafter will be considered exploratory (hypothesis-generating). The following sequence for secondary endpoint testing will be utilised: Proportion of CDAI remission at week 12 > CDAI low disease activity (≤ 10) at week 24 > CDAI low disease activity (≤ 10) at week 12 > ACR70% response at week 24 > ACR50% response at week 24 > Difference in change of patient global assessment > HAQ-DI > CRP at week 24 respectively. An early analysis of the main secondary endpoints will be performed at week 12. All other secondary outcomes will be analysed exploratorily.

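### The protocol contradicts itself on whether the primary outcome is assessed blind; on its plainest reading the evaluator global in CDAI ≤ 2.8 is scored unblinded, a bias that could be reduced but not removed

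*Protocol article*

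**What the plan says.** **Endpoint.** Under Statistical methods {27a}: "The primary endpoint, defined as the proportion of patients achieving CDAI remission at week 24, will be compared between treatment groups". Remission is CDAI at or below 2.8 (Table 1).

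**Components.** Data collection {25a} lists the disease-activity items as including "patient global assessment, evaluator global assessment, tender joints, swollen joints, CDAI". Table 2 schedules the EGA, the PGA and both joint counts at every visit. Neither place names the EGA rater.

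**Who is blinded.** Section {24a}: "Joint assessors performing outcome measurements are blinded to participants’ study assignments", and then "Patients, care providers and personnel performing randomisation are not blinded". The participant timeline {18} places the blinded assessor at every visit: "At each visit, a blinded joint assessment, patient reported outcomes as well as inflammatory and safety laboratory parameters are performed". The limitations paragraph of the Discussion is narrower: "patients and physicians are unblinded to the treatment allocation, and only joint assessment is performed by blinded personnel".

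**The statement that reads the other way.** Section {3d}: "No independent endpoint adjudication committee is planned, as outcome assessment is performed by blinded joint assessors according to predefined criteria".

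**Limits on the joint assessor.** Section {24b} gives this person no access to patient data or the eCRF, and allows no communication about study details with participants or unblinded staff.

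**The concern.** The Discussion confines blinding to the joint assessment. Section {3d} treats outcome assessment as a whole as blinded and relies on that to do without adjudication. A global rating by an evaluator is not a joint count, so for a CDAI endpoint the two statements cannot both be right.

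What is at stake is the primary comparison. The background section regards the evidence for s.c. superiority as a reasonable basis, and the trial hypothesises it, so any expectation would tend to favour s.c. Entry requires only CDAI above 2.8 with one swollen joint, so some participants can start close to the cut-off. The Discussion itself names variation in subjective disease activity as a limitation, especially in patients who start with low scores.

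**Working it through.** **1. The plan's own figure.** Inputs from Sample size {19}: 5% oral, 20% s.c., 80% power, two-sided alpha 0.05, χ² test, 16% dropout. The mean rate is (0.05 + 0.20)/2 = 0.125.

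n per group = [1.960·√(2·0.125·0.875) + 0.842·√(0.05·0.95 + 0.20·0.80)]² / 0.15² = (0.917 + 0.383)² / 0.0225 ≈ 75.1, so 76.

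76/0.84 = 90.5, so 91 per group and 182 in total. The stated figures reproduce, and nothing below changes them.

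**2. How much of the endpoint rests on the globals.** The article lists the four items but not the formula. I take the standard definition: CDAI = swollen joints + tender joints + PGA + EGA. With J the sum of the two joint counts, remission requires PGA + EGA ≤ 2.8 − J.

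| J | PGA + EGA must be at most |
|---|---|
| 0 | 2.8 |
| 1 | 1.8 |
| 2 | 0.8 |
| 3 or more | remission impossible |

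A single joint that is both swollen and tender counts twice (J = 2). The joint counts can therefore rule remission out but cannot establish it; every remission also depends on the two globals. How often the globals decide the result cannot be read from the documents.

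**3. Blinding by component.**

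| Component | Source according to the article |
|---|---|
| Swollen and tender counts | blinded joint assessor |
| PGA | unblinded patient |
| EGA | not named; unblinded by the Discussion, blinded by section {3d} |

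**4. What a differential shift would do.** The documents give no size for the bias, so the gaps are assumptions. Method: exact binomial enumeration with 91 per arm and the planned rule (χ², or Fisher's exact test if either group has fewer than five events). It sums the probability of all tables with p < 0.05 and more remissions on s.c. There is no true difference; the true rate is 12.5% in both arms.

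| Observed rate, oral / s.c. | Total gap | Patients (gap × 91) | P(false superiority of s.c.) |
|---|---|---|---|
| 12.5% / 12.5% | 0 points | 0 | 2.4% |
| 12.5% / 13.5% | 1 point | 0.9 | 3.8% |
| 12.5% / 14.5% | 2 points | 1.8 | 5.7% |
| 10.5% / 14.5% | 4 points | 3.6 | 12.2% |
| 9.5% / 15.5% | 6 points | 5.5 | 22.5% |

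The last two rows move the arms in opposite directions, by 2 and 3 points each. Splitting the 2-point gap in the same way (11.5% / 13.5%) gives 5.8%, so the split matters little there.

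**5. Other true rates, with the shift added to s.c. only.** At a true 5% in both arms, gaps of 2.5, 5 and 7.5 points give 5.9%, 18.6% and 38.5%, against 1.0% without bias. At a true 10% they give 7.2%, 16.8% and 30.8%, against 2.1%.

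All these gaps are for PGA and EGA together. Nothing in the documents allows the EGA's part to be separated.

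**The case against.** **The rater.** A reader might infer as fact that the unblinded treating physician scores the EGA. The article does not say so. Section {24a} speaks of joint assessors who perform outcome measurements, section {3d} credits them with outcome assessment, and the Discussion does not mention the EGA. The full protocol, which the article says is published with it, may name the rater and was not available here. This objection stands: unblinded scoring is the plain reading, not a stated fact. The contradiction remains either way, because if the EGA is blinded the Discussion is wrong.

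**Removal at no cost.** A reader might also infer that the bias could be removed without cost. It could not. The PGA comes from an unblinded patient, and open-label discontinuation feeds non-responder imputation. A blinded assessor already attends each visit, so no extra person appears necessary, but the limits in section {24b} mean the procedure must be defined, and an amendment takes time.

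**The size.** It would be wrong to read 12.2% or 22.5% as the effect of an unblinded EGA. Those figures rest on assumed gaps of 4 and 6 points from both globals; gaps of 1 to 2 points give 3.8% to 5.7%.

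**Disclosure.** The authors list open-label treatment as a limitation, and section {24a} defines who is blinded, so the assessor-blinded label is not false on its own terms. That is fair, but disclosure does not settle the contradiction with section {3d}, which relies on the weakness being absent.

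**Conclusion.** The point holds in limited form. The article contradicts itself on whether the primary outcome is assessed blind. Followed as the Discussion states it, the EGA enters CDAI ≤ 2.8 unblinded, leaving a directional bias that could be reduced.

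The conclusion rests on the standard CDAI sum and on the plain reading of section {24a} and the Discussion. The size is unknown. Under the assumed true rate of 12.5% in both arms of 91, total gaps of 1 to 6 points raise the false-superiority rate from 2.4% to between about 3.8% and 22.5%, with an unknown share due to the EGA. The sample size is unaffected. The point merits action while endpoint visits remain: the last first visit is planned for the end of November 2026 and the last visit for May 2027.

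**What to change.** 1. Reconcile section {3d} with the Discussion, and name the EGA rater.
2. For the efficacy CDAI, have the blinded joint assessor already present at each visit record the EGA on the joint-count source sheet. Other staff enter it in the eCRF, so the limits in section {24b} still hold. Keep any treating-physician global as a separate field.
3. Pre-specify a sensitivity analysis of week-24 response on the blinded joint counts alone. The documents supply no threshold, so fix one in advance; by the arithmetic above, only joint sums of 0, 1 or 2 are compatible with remission.
4. State that the PGA and open-label discontinuation remain open to bias.
5. For the CDAI-worsening criterion in section {15b}, state the source of its EGA consistently; nothing further is suggested there.

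**Cost.** An assessment instruction, an eCRF field, an analysis sentence and a protocol amendment (version 2.0, dated 16 May 2025, was approved on 11 August 2025). No extra staff appear to be needed. The EGA would be scored without chart data. Enrolment began in August 2024, so the EGA source would change mid-trial; apply the change identically in both arms and flag visits before and after it.

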## Trial status

The first approved protocol version 1.1 was from 28th March 2024. The latest approved version is 2.0 from 16th May, which was approved on 11th August 2025. The first patient was enrolled at the Medical University of Vienna on 12th August 2024. The first visit of the last patient is planned for the end of November 2026. The last patient’s visit is therefore expected to occur approximately 24 weeks later, in May 2027.

